### Design

The present study is a multicenter randomized stepped wedge trial. Patients with a DRF treated non-operatively and without performance of a closed reduction will be included in the study.

This stepped wedge trial will include 10 clusters, expecting to include 4 patients per cluster per time period of 4 weeks (Table 1). Every cluster will be randomized to a step: the moment when a cluster will start with the study. A transition period of one time period of 4 weeks is added between conditions A and B. This transition period is meant for explaining the treatment and to give instructions to the hospitals and caregivers to re-organize the treatment protocols.

**Table 1 Tab1:** Design Cast OFF-2, stepped wedge design

Cluster	T1	T2	T3	T4	T5	T6	T7	T8	T9	T10	T11	T12
1	A		B	B	B	B	B	B	B	B	B	B
2	A	A		B	B	B	B	B	B	B	B	B
3	A	A	A		B	B	B	B	B	B	B	B
4	A	A	A	A		B	B	B	B	B	B	B
5	A	A	A	A	A		B	B	B	B	B	B
6	A	A	A	A	A	A		B	B	B	B	B
7	A	A	A	A	A	A	A		B	B	B	B
8	A	A	A	A	A	A	A	A		B	B	B
9	A	A	A	A	A	A	A	A	A		B	B
10	A	A	A	A	A	A	A	A	A	A		B

*A*, usual care, 4–5 weeks of plaster cast treatment; *B*, 1 week of plaster cast treatment

An inclusion of 4 patients per cluster per month is expected. Before starting this study, every hospital needs to indicate the number of patients seen per month with a DRF who are treated non-operatively. Hospitals of which the expected number of patients will be less than 4 patients per month will be combined to one cluster. By adapting the study protocol based on the expected available patients, we expect that all clusters will reach sufficient inclusions.

Randomization will be performed to determine when a cluster will start with the study. The study period for every included patient will be 1 year. Follow-up of the included participants is the same for both groups: conditions A and B.

### Patient selection and methods

Patients with acute non-reduced DRFs (intra- and extra-articular DRF, non- and minimal displaced DRF) who are diagnosed at the emergency department will be included in the study. Patients need to be between the age of 18 and 85 years old, have an isolated non-reduced DRF and a good understanding of the Dutch language, and live independently.

Patients will be informed about the study at the emergency department. The treating physician will inform the patient about the study and provide them with written information about the study.

After 1 week, all patients will be seen at the hospital (plaster room outpatient clinic) for their first standard of care follow-up visit. During this visit (after 1 week at the plaster room), patients will be asked by the research team if they are willing to participate in the study. Patients need to give written informed consent for the use of their medical information and medical files and filling in questionnaires. The patients will be informed about the possibility that they will be called or emailed by the research team in case of incomplete or missing questionnaires during the 1-year follow-up.

The following inclusion and exclusion criteria will be used:

*Inclusion criteria*
Age between 18 and 85 yearsIsolated acute distal radius fracture; intra- and extra-articularClosed reduction is not performedNon-operative treatment with cast immobilizationAbility to perform activities of daily living (ADL) independentlyAbility to give informed consent

*Exclusion criteria*
Multiple injured patientReduction is indicated/performedOperative treatmentNo understanding of the Dutch languageA patient with extra care at home; in need of a caregiver or professional for ADLOpen fracturesHistory of surgically treated wrist fracture on the currently injured sideEstimated high risk of secondary displacement by the surgeon due to comorbidities, high risk of falling, or life circumstances

### Investigational treatment

All clusters will start simultaneous with their usual treatment: condition A. After 1 week of plaster cast, patients will be seen at the outpatient clinic, a physical examination will be performed, and a prolonged plaster cast will be provided (another 2–4 weeks).

During the second follow-up visit at the outpatient clinic, the plaster cast will be removed, the duration of immobilization with the plaster cast will be registered, a physical examination will be performed, and extra questions on function and pain will be asked. After removal of the plaster cast, information is given about the importance of using their arm and performing the exercises of the home exercise program.

When the cluster/hospital is randomized to switch treatment, all patients will be treated following condition B. Patients in condition B will have an immobilization period of 1 week. Patients will get a splint or cast at the emergency department. After 1 week, an appointment is scheduled at the outpatient clinic. Instead of a plaster cast change, the splint or cast will be removed and physical examination will be performed. After the removal of the plaster cast, information is given about the importance of using their arm and doing the exercises of the home exercise program. Four to 5 weeks post-injury, patients will have a second follow-up appointment at the outpatient clinic where a physical examination will be performed and additional questions on function and pain will be asked. When patients did not give informed consent for use of their medical files and filling in questionnaires, they will still be treated by the protocol the hospital is using at that moment. That can be condition A or B.

### Measurements

For this study, the following main study parameters are gathered: functional outcome, return to activity, cost-effectiveness, and acceptability of the study protocol.
Patient-reported outcome (functioning and patient satisfaction): It is known that 1 week of plaster cast for a non-reduced DRF is safe. Secondary displacement of the fracture is not significantly different with longer plaster cast treatment [8, 9]. So, the most important question is whether 1-week treatment gives better functional results and higher patient satisfaction. The best measurement method to measure patient satisfaction and functional result is using a patient-reported outcome (PRO) [14]. In addition, PROs are better predictors of participation, such as the ability to return to work or perform daily activities, than more objective clinical measures.The Patient-Reported Wrist Evaluation (PRWE) is specifically designed for wrist and hand functioning. The PRWE is a reliable and valid measure of patient-rated pain and disability for wrist conditions [15, 16]. Furthermore, a validated Dutch version of the questionnaire is available [17]. The PRWE is a measurement with a score from 0 to 100, where 0 is no wrist function problems or pain. The minimal clinical important difference for PRWE is a difference of 11 points [18].The questionnaires will be sent to the patient after 6 weeks and 3, 6, and 12 months.Return to activity will be measured using the productivity costs questionnaire (iCPQ). Questions about return to work, leisure activities, household activities, and pain will be asked. These questions will be asked after 1 and 6 weeks, 6 months, and 1 year.A cost-effectiveness analysis will be performed alongside the stepped wedge trial. The Health care Institute of the Netherlands (ZIN) 2016 guideline for economic evaluations forms the basis of the analysis [19]. Healthcare consumption from inclusion to final follow-up of the patient is measured. This is in line with the measurement pathway of the clinical study. Healthcare consumption is multiplied by unit costs associated with healthcare consumption. Also, productivity-related costs seem to play an important role. Therefore, the societal perspective is the base case. A healthcare perspective is used as the scenario. These will be measured using a selection of questions of the medical consumption questionnaire (iMCQ) and the productivity costs questionnaire (iCPQ). These questions will be asked after 1 and 6 weeks, 6 months, and 1 year. The costs and for example months not working will be compared for the two different condition groups.Acceptability of the study protocol. Measuring the actual time of plaster cast treatment and number of patients who followed the protocol. If not following the protocol (condition A or B), reason for violation of the protocol. The answers to these questions will be gathered at the end of the study by provided information from the hospitals and questions asked to the participating physicians. All patients who gave informed consent will be checked if they follow the correct protocol. If they did not follow the protocol, information will be gathered why the protocol was not followed. Additionally, questions will be asked to the participating centers (local head of research). The questions asked are about feedback to the study, if they will implement the interventional treatment, why they will or will not implement the treatment, what changes to the treatment they would make, etc. The number of protocol violations and comments will be compared for both groups.

The following secondary parameters will be measured.
Complications. The complication checklist for DRF from McKay will be used for scoring the complications after a DRF [20]. The clinical record and questionnaire will be used to complete the checklist from McKay. The Budapest diagnostic criteria will be used to score CRPS, a complication which can occur after a DRF [21]. In addition, pain and post-traumatic pain will be scored. The visual analogue scale (VAS) will be asked, and the PROMIS questionnaire will be used for pain interference and diagnosing post-traumatic pain [11, 22]. In addition, we will measure the use of pain medication by using the iMCQ and iCPQ. Figure 1 shows the moment when these parameters are gathered.

**Fig. 1 Fig1:**
[figure not shown]
Time schedule for the included patients of the Cast OFF-2Comprehensive PRO measures will be gathered. This is a more generic instrument that captures aspects of health status and quality of life beyond hand functioning. The questionnaire is useful to identify the contribution to overall disability. The EuroQol-5 dimensions 5-level questionnaire (EQ-5D-5L) [23]. This questionnaire is sent after 6 weeks and 3, 6, and 12 months post-injury.Patient satisfaction will be additionally measured by using a 10-point ordinary scale, 0 is not satisfied with the treatment and 10 is very satisfied with the treatment. As this is an interesting question but not a validated question for wrist fractures, the minimal important clinical difference is not known. The difference between the groups will be analyzed. The questions will be asked after 6 weeks and 3, 6, and 13 months.A budget impact analysis will be performed from various perspectives with the budgetary framework for the care as the base case perspective (budgettair kaderzorg). Here too, the ZIN 2016 guideline serves as a starting point for the analysis. The analysis will be performed in accordance with the ISPOR Principles of Good Practice for Budget Impact Analysis [24].

The following other study parameters such as demographic and clinical data will be collected to measure the association with the above-mentioned outcome parameters.
Age at inclusionGenderSide of fractureSide of the dominant handSmokingUse of pain medication, if yes which pain medication and dose at inclusionVAS score at inclusionUse of vitamin CWork or retired and specifiedDuration not able to work or perform household activitiesLeisure activitiesFracture classification using AO classification systemPain catastrophizing scale (PCS-4) will be used to measure patients’ fear for movement and the influence of psychological problems [25]Use of physiotherapy, asked after 1 yearUse of home exercise programComorbidities using Cumulative Illness Rating Scale (CIRS)

### Follow-up

The follow-up of the included patient will be the same for both groups, conditions A and B. All questionnaires will be sent via email. The follow-up will take place per participant/patient. The patients will be informed about the possibility that they will be called or emailed by the research team in case of incomplete or missing questionnaires during the 1-year follow-up.

Patients will be informed about the importance of finishing the questionnaires and will be called or contacted via email if they did not complete the questionnaires.

#### Outpatient clinic follow-up

The outpatient clinic follow-up will take place after 1 week and 4–5 weeks. During these visits, several questions about pain and performing activity will be asked.

#### Pain and activity

The pain catastrophizing scale will be sent 6 weeks post-injury and 3, 6, and 12 months post-injury [25]. After 4–5 weeks, these questions will be asked as part of the routine outpatient clinic visit.

#### Cost-effectiveness and work ability

A selection of the medical consumption questionnaire (iMCQ) and the productivity costs questionnaire (iCPQ) will be sent 1, 6 weeks, and 6 months post-injury. The questions which are not useful for the study, such as questions about occupational therapist appointments or a dietician appointment, were discarded. The general questions from both the questionnaires are the same, and these were combined into one questionnaire.

At the end of the study, 1 year post-injury, these questions will be asked again.

#### Patient-reported outcome

All of the following questionnaires will be sent 6 weeks and 3, 6, and 12 months post-injury.
Patient-Rated Wrist Evaluation (PRWE) score [17]EQ-5D-5L [23]PROMIS Pain Interference (PROMIS PI)Visual analogue scale for pain and patient satisfaction (VAS)

#### Complications

Complications will be scored, 6 weeks and 3, 6, and 12 months post-injury.

The following will be scored:
Secondary displacementMcKay complication checklist [20]Budapest criteria for scoring CRPS [21]

#### Evaluation of implementing 1 week of plaster cast immobilization

After 1 year, when the inclusion period ends, all participating centers will be asked to fill out an evaluation form. This evaluation form will include questions such as if they prefer condition A or B, if condition B will be used as a new protocol in their hospital, feedback for the study, and changes for the protocol of condition A.

Figure 1 shows the time schedule for the used questionnaires.

### Time schedule

Inclusion of 440 patients will take place during a 1-year time period in the participating medical centers. A follow-up period of 12 months is taken into account and 6 months for data analysis and publication. See Fig. 1.

### Power analysis

We used the stepped wedge sample size tool in STATA.

A sample size of 330 patients was calculated with a power of 0.85, alfa of 0.05, and *ICC* of 0.01. We designed the stepped wedge for ten clusters with three patients per cluster per time period (Table 1). We used results from our pilot study for the reference values. The Patient-Rated Wrist Evaluation (PRWE) scores after 6 weeks were used as this will be one of our most important outcomes and have a validated clinical difference score. We used a PRWE score of 35 for the control group and 25 for the intervention group. A difference of around 10 points is needed to reach a relevant clinical difference [18]. In order to account for a 30% loss to follow-up, we aim for a sample size of 440 patients, i.e., four patients per cluster per time.

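### The target of 440 patients covers a 25% loss to follow-up, not the 30% that the Power analysis section states

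*Protocol article*

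**What the plan says.** The Power analysis section sets the evaluable sample: "A sample size of 330 patients was calculated with a power of 0.85, alfa of 0.05", with an intracluster correlation (ICC) of 0.01. The layout behind that number is given there too: "We designed the stepped wedge for ten clusters with three patients per cluster per time period (Table 1"). The planning values are PRWE scores of 35 under usual care and 25 under the intervention at 6 weeks, taken from the pilot study. The allowance for attrition follows: "In order to account for a 30% loss to follow-up, we aim for a sample size of 440 patients", described as four patients per cluster per period.

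The Abstract, the Time schedule section and the Discussion repeat 440 without any further derivation. The Design section explains why each cluster contributes 11 of the 12 periods: "A transition period of one time period of 4 weeks is added between conditions A and B".

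On the size of a relevant PRWE difference, the Power analysis section says "A difference of around 10 points is needed to reach a relevant clinical difference", while the Measurements section says "The minimal clinical important difference for PRWE is a difference of 11 points". Both cite the same reference.

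**The concern.** Three figures are given as holding together: 330 patients needed, 30% lost, 440 recruited. Any two of them fix the third, and the third does not agree. The sample that must remain after loss is 330, so the recruitment target should be 330 divided by the proportion retained. The target of 440 is smaller than that.

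What is at stake is the attrition allowance that the article claims. Someone judging retention during or after the trial would take any loss up to 30% as provided for. At a loss of 28%, for example, the text implies that the required sample is intact, yet 440 × 0.72 = 316.8, so about 317 patients remain, already below 330.

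**Working it through.** **Inputs from the protocol article.** Required evaluable sample 330, power 0.85, alpha 0.05, ICC 0.01, PRWE 35 versus 25 (difference 10), loss 30%, target 440 (all from Power analysis); 10 clusters, 12 periods, one blank transition period per cluster (Design, Table 1).

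**Step 1. Reproduce the plan's totals.** Each cluster has 12 − 1 = 11 counted periods, so Table 1 has 10 × 11 = 110 counted cells, 55 under A and 55 under B.
- 110 × 3 = 330, as stated.
- 110 × 4 = 440, as stated.

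Both totals rest on 11 periods, so the blank transition cells hold no reserve.

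**Step 2. Check the attrition allowance.**
- Remaining after 30% loss: 440 × (1 − 0.30) = 308, which is 330 − 308 = 22 short, or 308/110 = 2.8 per cell.
- Largest loss that 440 absorbs: 1 − 330/440 = 0.25.
- Recruits needed for 30% loss: 330/(1 − 0.30) = 471.4, so 472, which is 472 − 440 = 32 more than planned.

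A possible origin of 440 is multiplication instead of division: 330 × 1.30 = 429, or 429/110 = 3.9 per cell, rounded up to 4. A plain step from 3 to 4 per cell gives the same total. The article does not say which was done.

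**Step 3. What it could mean for power.** This step needs the total SD of the PRWE, which the article does not give. It uses the usual stepped-wedge mixed model on Table 1: a fixed effect for each period, a random cluster effect with variance ICC × SD², a cell-mean error variance of (1 − ICC) × SD²/m for m patients per cell, and blank transition cells. Two-sided alpha is assumed. Power = Φ(10/SE − 1.96), where SE is the generalised least squares standard error of the treatment effect.

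Solving for the SD that gives 0.85 at m = 3 yields 19.997, in effect 20. At SD 20:

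| Patients per cell | Total | SE | Power |
|---|---|---|---|
| 3 | 330 | 3.34 | 0.850 |
| 2.8 | 308 | 3.44 | 0.827 |
| 4 | 440 | 2.93 | 0.926 |

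When the SD is recalibrated each time so that 330 patients give exactly 0.85, power at 308 stays between 0.825 and 0.830. The variants tried were no transition period, no period effects, one-sided alpha, and ICC from 0 to 0.10.

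**Step 4. If 0.85 was a target rather than the power achieved.** Whole patients per cell must be chosen. In the same model, two per cell reach 0.85 only if the SD is about 16.6 or less, and three per cell reach it up to about 20.0. So three per cell is the smallest whole number that meets 0.85 for any SD from about 16.6 to 20.0. At 2.8 per cell, power is 0.85 or more when the SD is about 19.4 or less. At SD 18, for example, it is 0.914 with 330 patients and 0.897 with 308.

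**The case against.** A reader might infer that the trial falls short of its stated power, or that power at 30% loss is 83%. The article does not support either as fact. It does not say whether 0.85 is the power achieved with three per cell or the level aimed at before rounding up to whole patients. If it was the aim, rounding up may have left enough slack for 308 patients to reach 0.85. An SD of 20 is plausible because the back-solve lands on a round number, but it is still inferred. This argument stands, and it makes any power figure conditional. It does not touch the comparison of 308 with 330.

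Other points limit the consequence. The planning outcome is the PRWE at 6 weeks, the first PRWE questionnaire, while follow-up runs to 12 months. The 30% is not tied to a time point, so loss at 6 weeks may be lower. The Statistical analysis section plans a mixed model with repeated measurements and some multiple imputation, so a missed questionnaire need not remove a patient from the analysis. The Methods section also lists acceptability as the primary outcome and the PRWE as secondary, although the Discussion calls the PRWE the primary outcome measure. All this may soften the effect. None of it makes 440 sufficient for the 30% that the article itself says is covered.

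A reader might also see a contradiction in the PRWE threshold, so that a 10-point result would be relevant by one section and not by the other. That goes too far. The Power analysis section says only around 10, and no section sets a success or responder rule on either value. Planning on 10 is also the more cautious choice for power: at SD 20, an 11-point difference gives about 0.91 with 330 patients and 0.89 with 308.

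Finally, the absence of the SD is not a fault here. A condensed article may leave it to the full protocol or analysis plan.

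**Conclusion.** The statement in the Power analysis section is wrong as written. From the article's own figures and with no assumption, 440 recruits cover at most 25% loss; at 30% they leave 308, which is 22 below the 330 required, and 472 would be needed. No other section repairs this.

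The effect on power is modest at most and cannot be fixed from the article. With an assumed SD of 20, it falls by 0.850 − 0.827 = 0.023, to about 0.83. With an SD of about 19.4 or less, the stated 0.85 still holds at 308. Both figures assume two-sided alpha, ICC 0.01 and loss spread evenly over the cells of Table 1. The point warrants a correction to the text and is no reason to doubt the design. The difference between around 10 and 11 PRWE points is editorial.

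**What to change.** In the Power analysis section, do one of the following:

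- Keep the target of 440 and state that it allows for 25% loss to follow-up.
- Keep the 30% and state the power for 308 evaluable patients, computed by the sponsor from its own pilot SD. The 0.83 above should not be copied into the protocol, because it rests on an inferred SD.

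Separately, give the relevant PRWE difference in the same form in the Measurements and Power analysis sections.

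The cost is a few words and, for the second option, one rerun of the sample size tool. No extra recruitment or change in conduct is needed. The stated attrition allowance, or possibly the stated power, becomes slightly less favourable.

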### Randomization

Each cluster will start with the usual care: condition A. The clusters/hospitals will be randomized for when to start with condition B. Patients are not randomized but follow the condition in their hospital. Castor will be used for randomizing the clusters. The clusters will be blinded only for the timing when they will start with the treatment of 1-week plaster cast immobilization: condition B. The researcher who will perform the randomization through castor will let the clusters/hospitals know when to start with condition B. At the beginning of the study, all hospitals will be informed about when they will switch from condition A to B. The data analysts will be blinded for the randomization of the clusters and when every cluster starts with condition B.

